## 6. Study Design

### 6.1. Intervention Regimens

The study design describes a single-centre, randomised, placebo-controlled, two-arm study (see Figure 1). The experimental (intervention) strategy will be to perform PGT-A via NGS on good-quality embryos at the fully expanded blastocyst stage.

### 6.2. Timing of Randomisation

Randomisation will occur on day 3 following egg collection. At this point, all consented patients will be evaluated for eligibility. Specifically, patients will be randomised if they have at least three good-quality embryos, as assessed using the embryo-scoring system of the Association of Clinical Embryologists (UK).

### 6.3. Care Pathway Post-Randomisation

Women in the control arm will proceed with a fresh embryo transfer procedure on day 5 following egg collection, or, if clinically indicated, a frozen–thawed embryo transfer as first-line treatment over a fresh transfer. Women in the experimental arm will have PGT-A performed from trophectoderm biopsy on embryos that reach the blastocyst stage, which typically occurs on days 5, 6, or 7 following egg collection.

All embryos will be frozen after the biopsy procedure. The CCS of all chromosomes will be performed using NGS and embryos will be categorised as euploid, mosaic aneuploid, and aneuploid embryos. Mosaic embryos will be ranked based on the degree of aneuploidy (low- and high-mosaic aneuploid embryos).

A low-mosaic embryo is defined as an embryo with whole-chromosome aneuploidies in 30–50% of the biopsied cell and a high-mosaic embryo is defined as an embryo with whole-chromosome aneuploidies in 50–70% of the biopsied cells.

### 6.4. Embryo Transfer

Only single-euploid embryos or low-mosaic embryos that are deemed suitable to be replaced, with prioritisation based on the morphological grading of the embryos, will be transferred in subsequent frozen–thawed embryo transfer cycles, which could be initiated as early as with the next menstrual cycle following egg collection. Euploid embryos will preferably be transferred to low-mosaic embryos and the couple will need to undergo genetic counselling before transferring a low-mosaic embryo.

The subsequent frozen–thawed embryo transfer (FET) of a single-euploid embryo will occur either in a natural cycle or a hormonally medicated cycle using physiological doses of oestrogen and progestogens to prepare the endometrium.

If patients decide not to transfer mosaic embryos, these instances will be thoroughly documented, including the reasons and clinical factors involved. These data will be incorporated into the study through descriptive analysis, which will outline the frequency of and reasons for these decisions. Additionally, sensitivity analyses will assess how excluding mosaic embryos affects the study outcomes, ensuring that the results accurately reflect both the protocol and real-world practices. The final report will address the implications of transferring versus not transferring mosaic embryos on the study’s primary and secondary endpoints, providing a comprehensive understanding of their impact.

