## 1. Introduction

### 1.1. Background

The selection of the most viable embryo is typically based solely on light microscopy and morphological assessment in assisted reproductive technologies (ART) [1,2,3]. However, despite significant technological and scientific advances in the field, many women still fail to achieve clinical pregnancy or live birth, despite the transfer of embryos classified as good quality by various guidelines [4,5,6,7,8]. This high rate of failure is believed to due to the limitations of relying solely on morphological evaluation, which is an inefficient method of determining embryo ploidy, unable to accurately distinguish between euploid, aneuploid, or mosaic embryos, which have distinct implantation potentials [3,7,8]. The human embryo aneuploidy rate is reported to range between 30% and 50% when under 35 years of age and to increase to 80% in patients aged 42 years of age or older [9,10], reflecting the higher miscarriage rates and lower live birth rates often seen in women of advanced reproductive age. Often, to increase the chances of a live birth, assisted-conception units rely on the transfer of multiple embryos graded as good on morphological criteria alone. However, multiple-embryo transfer is known to increase the risk of multiple pregnancies, which are associated with significant foetal, maternal, and neonatal risks, as well as long-term complications [11]. In view of this, providing patients with an added level of single-embryo selection beyond a static or dynamic morphologic evaluation is of increasing clinical importance.

Preimplantation genetic testing for aneuploidies (PGT-A), combined with next-generation sequencing (NGS), aims to identify and transfer euploid embryos with the highest implantation potential, while excluding aneuploid embryos that are likely to arrest in development and lead to negative pregnancy outcomes [12,13,14]. In additional to shortening the time-to-pregnancy timeline, reducing the miscarriage rate, and improving live birth rates, IVF with PGT-A also aims to promote single-embryo transfer, thereby reducing the risk of multiple births without lowering overall IVF success rates [13,15].

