### 2.1. Objective

In the proposed pilot study, we will evaluate recruitment, randomisation, and adherence to study protocol and allocated trail arms by participating women. We aim to incorporate the results of the pilot study into the main RCT, for which ethical approval will be sought. Participating women will be informed of our intention to include the pilot data in the full study.

The purpose of the RCT will be to determine if a policy of embryo selection and transfer based on morphological evaluation and PGT-A with NGS is a more clinically effective, safer, more cost-effective, and acceptable way to provide IVF treatment in women of advanced reproductive age compared to the routine practice of embryo selection and transfer based on morphological evaluation alone.

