### 7.2. Handling Participants Who Do Not Follow Their Allocated Arm

Participants who do not adhere to their allocated study arm will be tracked through the study’s monitoring system. Reasons for non-compliance will be documented, and alternative approaches will be considered to account for deviations in the final analysis. Non-compliance will also be recorded and assessed to understand its impact on study outcomes. The analysis will include intention-to-treat (ITT) and per-protocol approaches to evaluate the effect of treatment allocation versus the actual received treatment.

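### Excluding mosaic embryos can change the PGT-A arm only, so the planned sensitivity analysis is not a randomised comparison, and its direction depends on the endpoint and denominator

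*Protocol article*

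**What the plan says.** Section 6.3 describes testing for one arm: "Women in the experimental arm will have PGT-A performed from trophectoderm biopsy on embryos that reach the blastocyst stage". For the other arm it describes no biopsy or sequencing: "Women in the control arm will proceed with a fresh embryo transfer procedure on day 5 following egg collection", or a frozen transfer where clinically indicated. Section 2.1 describes the comparator as the "routine practice of embryo selection and transfer based on morphological evaluation alone". Section 1.1 says that morphological evaluation is "unable to accurately distinguish between euploid, aneuploid, or mosaic embryos, which have distinct implantation potentials".

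Section 6.4 sets the order of use in the PGT-A arm: "Euploid embryos will preferably be transferred to low-mosaic embryos". It then deals with refusals: "If patients decide not to transfer mosaic embryos, these instances will be thoroughly documented, including the reasons and clinical factors involved". These are to be described by frequency and reason. In addition, "sensitivity analyses will assess how excluding mosaic embryos affects the study outcomes", and the section presents this as a means of making the results a faithful picture of both protocol and routine care. No unit (embryo, transfer or woman), denominator or rule for women with only mosaic embryos is given, nor whether the result is to be set against the control arm.

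Section 5 lists clinical pregnancy both per transferred embryo and per randomised woman. Section 7.2 keeps the main analysis sets: "The analysis will include intention-to-treat (ITT) and per-protocol approaches". Section 9 places low-mosaic embryos after euploid ones in its ranking by implantation potential.

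**The concern.** Control women will also receive mosaic embryos, but nobody will know which ones. An instruction to exclude mosaic embryos can therefore be carried out in the PGT-A arm and has no counterpart in the control arm. The selection rests on a test result that arises after randomisation and, where refusals are involved, on a patient's choice made in the light of that result. Because euploid embryos are preferred, a low-mosaic transfer goes mainly to a woman with no euploid embryo available, so those removed are not a random subset of the arm. Randomisation does not protect a comparison of the remainder with an intact control arm.

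The underlying question, what a euploid-only transfer policy would have achieved, is a sensible one. An exclusion does not answer it, because under such a policy these women would still be in the trial, without that transfer. The answer matters beyond this one table: mosaic outcomes are part of the study's claimed novelty (section 1.2), section 7 lets promising preliminary results bear on continuation, and section 2.1 intends the pilot data to be incorporated into the main RCT.

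**Working it through.** The article gives no figure for this analysis, so there is none to reproduce. The check is a reading of the sections together, followed by an illustration with assumed rates.

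**Which arm can change.** Testing is described in the experimental arm only (6.3). Control selection is by morphology alone (2.1), and morphology cannot identify mosaics (1.1). No control embryo carries a mosaic label, so the control rate shifts by exactly 0 under any exclusion rule. Only the PGT-A rate can move.

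**Inputs from the article.** 100 women (6.7) and 1:1 allocation (2.8), so about 50 per arm.

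**Assumed inputs.** One counted transfer per woman. *E* women have a euploid transfer, *M* a low-mosaic transfer only, and *O* no transfer, with *E* + *M* + *O* = 50. Pregnancy rates per transfer are *s_e* (euploid) and *s_m* (low-mosaic).

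**Formulas for the PGT-A arm.**
- Per transferred embryo, all: (*E*·*s_e* + *M*·*s_m*)/(*E* + *M*). Mosaics excluded: *s_e*.
- Per randomised woman, all: (*E*·*s_e* + *M*·*s_m*)/50. Recipients dropped: *E*·*s_e*/(50 − *M*). Recipients kept, their pregnancies not counted: *E*·*s_e*/50.

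**One worked case.** *E* = 35, *M* = 5, *O* = 10, *s_e* = 50%, *s_m* = 30%.
- Per transferred embryo: (17.5 + 1.5)/40 = 47.5% becomes 50.0%, or +2.5 points.
- Per randomised woman: 19/50 = 38.0% becomes 17.5/45 = 38.9% (+0.9) if recipients are dropped, or 17.5/50 = 35.0% (−3.0) if they are kept and not counted as pregnant.

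**Range.** With *s_e* = 50%, *M* from 3 to 10 and *O* from 5 to 15:

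| Version | *s_m* 20–40% | *s_m* 50% | *s_m* 60% |
|---|---|---|---|
| Per transferred embryo, mosaics excluded | +0.7 to +8.6 points | 0 | −0.7 to −2.9 |
| Per woman, recipients dropped | −1.8 to +4.7 | negative | negative |

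Per woman with recipients kept and their pregnancies not counted, the shift is always negative: −1.2 to −12.0 points across all these values of *s_m*.

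**Why the per-woman sign is open.** Dropping recipients raises the rate only if their own pregnancy rate is below that of the whole arm, and the whole arm includes women with no transferable embryo and hence no pregnancy. Take 20/50 = 40% pregnant and 8 low-mosaic recipients (assumed). Break-even is 0.40 × 8 = 3.2 conceptions.

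| Recipients who conceived | All women | 8 dropped | 8 kept, not counted |
|---|---|---|---|
| 2 of 8 | 20/50 = 40.0% | 18/42 = 42.9% | 18/50 = 36.0% |
| 4 of 8 | 20/50 = 40.0% | 16/42 = 38.1% | 16/50 = 32.0% |

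In the first row the same data show a gain of 2.9 points under one rule and a loss of 4.0 under the other.

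**The case against.** The strongest reply is that section 6.4 speaks of excluding embryos, not women, and names no between-arm test. Its paragraph opens with patients who decline a mosaic transfer. It could mean a look within the PGT-A arm, or even the euploid-only analysis recommended here. A condensed article may leave the denominator to an analysis plan. This stands in part: the missing denominator is not itself a fault, and nobody can say that the plan commits to dropping women. It does not remove the point. No later choice of denominator gives control embryos a mosaic label, and the article claims that the analysis safeguards the accuracy of results on the study outcomes, which is broader than a within-arm description.

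A reader might infer that the exclusion tilts every outcome towards PGT-A. The documents do not support that. The tilt follows for the per-embryo rate under the article's own ranking. Per randomised woman it depends on an unstated rule and on a low-mosaic pregnancy rate that the article does not give, and it can go against PGT-A. Low-mosaic recipients are also not the worst-prognosis group, since women with no transferable embryo fare worse and stay in the denominator.

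A reader might also infer that the final report will rest its conclusions about mosaic transfer on this exclusion. Section 6.4 says only that the report will address the matter, and descriptive reporting of refusals is already planned.

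Lastly, the stakes are limited. ITT is kept, the primary outcome is feasibility, and section 2 disclaims definitive conclusions on pregnancy rates.

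**Conclusion.** The concern holds as a one-arm, post-randomisation exclusion. That part rests on the article's text alone and needs no assumed rates. Any version that drops mosaic embryos or their recipients is not a randomised comparison and cannot deliver the accuracy that section 6.4 claims for it.

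The size and direction rest on assumptions. Per transferred embryo, the PGT-A rate rises by 0.7 to 8.6 points for low-mosaic rates of 20–40% against 50% for euploid, with no shift in control; it would not rise if low-mosaic embryos did as well as euploid ones. Per randomised woman no general direction can be claimed.

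This should be corrected, but it is a weakness of a supplementary analysis and does not touch the ITT comparison or the feasibility outcome.

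**What to change.** In section 6.4 and the analysis plan:

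1. State that mosaic status is known in the PGT-A arm only.
2. Define the between-arm sensitivity analysis as a euploid-only analysis on all randomised women. Every PGT-A woman stays in the denominator, a pregnancy from a low-mosaic transfer is not counted, and the control arm is unchanged. Report it beside the ITT result.
3. Label any analysis that drops mosaic embryos or their recipients as descriptive within the PGT-A arm, with no between-arm test. Keep the planned description of low-mosaic transfers and refusals.
4. Remove the claim that the exclusion ensures accurate results.

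The cost is a few sentences and no new data. There is one small downside: the euploid-only figure is conservative for PGT-A, because a later euploid transfer that might have been used instead is not credited. This should be said when it is reported. The change is an analysis rule only and alters no clinical management.

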### 6.5. Pregnancy Outcome

A pregnancy test will be undertaken around 2 weeks after the embryo transfer in all women. If the pregnancy test is negative, this will be the endpoint for the pilot study for these participants. If the pregnancy test is positive, women will routinely undergo an ultrasound scan after a further 3 weeks to identify the presence of clinical pregnancy, which will be the endpoint for the pilot study for these participants.

Women are requested to report the outcome of the pregnancy, which is a routine practice by all UK clinics, as it is a mandatory requirement for clinics to report IVF treatment outcomes to the Human Fertilisation and Embryology Authority (HFEA), which is the statutory regulator for all assisted-reproduction treatments performed in the UK. Women will be contacted to follow-up the outcomes if they fail to contact the IVF clinic.

Participants will be informed of this and consent to being followed up and to the use of the data from the pilot phase if the study progresses to the full stage. Data on all baseline characteristics and outcomes will be collected using a standardised electronic case report form (eCRF).

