## 5. Secondary End Points

The following secondary outcomes will be recorded:Clinical pregnancy rate per transferred embryo.Clinical pregnancy rate per randomised woman.Miscarriage rate per transferred embryo.Time to pregnancy leading to live birth.

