### 6.7. Statistical Considerations

#### Sample Size

For this pilot feasibility randomised controlled trial, a sample size of 100 women was determined. Patients will be recruited to the study at their initial consultation at the fertility clinic, and further recruitment will continue through their monitoring scans until the day of egg collection. Additional centres may be involved in the full study if it goes ahead. This sample size allows us to estimate recruitment rates with a margin of error of ±10.5% around the true rate, providing an 80% confidence interval. While formal hypothesis testing is not the primary focus of this pilot study, an alpha value of 0.05 (5%) and a beta value corresponding to 80% power (β = 0.2) would be considered standard if a preliminary hypothesis testing were conducted [26]. Given the strict regulatory framework governing IVF in the UK, particularly the mandatory reporting of all IVF treatment outcomes, as required by the Human Fertilisation and Embryology Authority (HFEA), we anticipate nearly complete follow-up, approaching 100%.

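### The pilot's stop at a negative pregnancy test conflicts with the secondary endpoint of time to a pregnancy leading to live birth, because no follow-up of later transfers is stated

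*Protocol article*

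**What the plan says.** Section 6.5 sets two stopping points. After a test about two weeks after transfer: "If the pregnancy test is negative, this will be the endpoint for the pilot study for these participants". After a positive test, a scan follows three weeks later "to identify the presence of clinical pregnancy, which will be the endpoint for the pilot study for these participants".

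Section 5 lists "Time to pregnancy leading to live birth" and "Miscarriage rate per transferred embryo" among the secondary endpoints. The list of strengths and weaknesses at the end of the Discussion repeats both in substance.

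Section 6.5 goes on to describe outcome reporting: "Women are requested to report the outcome of the pregnancy, which is a routine practice by all UK clinics". It adds: "Women will be contacted to follow-up the outcomes if they fail to contact the IVF clinic". Section 6.7 points to mandatory reporting to the regulator and says "we anticipate nearly complete follow-up, approaching 100" per cent.

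Other relevant provisions:
- Section 6.2 requires three or more good embryos on day 3 before randomisation.
- Section 6.3 gives controls a fresh day-5 transfer, or a frozen one where clinically indicated.
- Sections 6.3 and 6.4 freeze all biopsied embryos and refer to later frozen–thawed cycles in the plural.

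**The concern.** A time-to-live-birth-pregnancy endpoint needs each woman to be observed until she conceives such a pregnancy or until a common cut-off. The stop at a negative test ends observation because a transfer failed. Since the entry rule makes surplus embryos likely, a later transfer from the same egg collection could still succeed, and nothing says it would be recorded for the pilot.

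This matters for the comparison because PGT-A changes the order in which embryos are transferred and removes some of them. Looking only at the first transfer counts the gain from ordering and leaves out what the control arm's remaining embryos would have given. The Abstract's own rationale is that women need many transfers and so wait longer for a live birth; a first-transfer stop cannot show that.

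The consequence reaches beyond the pilot. Section 2.1 intends to carry pilot data into the main trial, and Section 7 lets promising preliminary trends inform continuation. Later transfers that are not captured as they happen may be hard to recover consistently.

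**Working it through.** **Reading the sections together.** The pilot stops at about 2 weeks after transfer (negative test) or 2 + 3 = 5 weeks (positive test, then scan). Neither point reaches a live birth.

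| Event needed for the secondary endpoints | Stated route |
|---|---|
| Miscarriage or live birth after a positive scan | Yes: reporting and active contact (6.5), mandatory reporting (6.7) |
| Later transfer after a negative test | None stated |
| PGT-A woman with no embryo to transfer | Documented as a deviation (7.3), but no pilot endpoint is set for her |

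**Size of the effect.** The plan gives no figure for this endpoint, so the following is an illustration with assumed inputs.
- k = blastocysts per woman, varied from 1 to 3.
- e = euploid share, 0.20 to 0.50. The Introduction quotes aneuploidy of 30–50% under age 35 and 80% at 42 or older.
- q = live-birth pregnancy per euploid transfer, 0.4 to 0.6.
- Aneuploid transfers never succeed, the test is perfect, biopsy does no harm, and there is no mosaic category.

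Formulas:
- First transfer, control: e·q
- First transfer, PGT-A: [1 − (1 − e)^k]·q, which counts women with no euploid embryo as failures
- All transfers, either arm: 1 − (1 − e·q)^k

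With k = 3, e = 0.35, q = 0.5:
- Control, first transfer: 0.35 × 0.5 = 17.5%
- PGT-A, first transfer: (1 − 0.65³) × 0.5 = 0.7254 × 0.5 = 36.3%
- Both arms, all transfers: 1 − 0.825³ = 43.8%

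The apparent gain is 18.8 points where the cumulative difference is zero. Over the grid k = 2–3, e = 0.20, 0.35, 0.50 and q = 0.4, 0.5, 0.6, the apparent gain runs from 6.4 to 22.5 points. With k = 1 both first-transfer rates equal e·q, and the difference is zero.

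**On the time scale.** Assume a control fresh transfer on day 5, the first frozen transfer in either arm on day 45, further transfers every 60 days, and time capped at 365 days. Women without success count as 365.
- First transfer only, control: 0.175 × 5 + 0.825 × 365 = 302 days
- First transfer only, PGT-A: 0.3627 × 45 + 0.6373 × 365 = 249 days
- All transfers, control (days 5, 45, 105): 0.175 × 5 + 0.1444 × 45 + 0.1191 × 105 + 0.5615 × 365 = 225 days
- All transfers, PGT-A (days 45, 105, 165): 0.3627 × 45 + 0.0704 × 105 + 0.0054 × 165 + 0.5615 × 365 = 229.6 days; a simulation of 400,000 women per arm gave 229

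PGT-A looks 53 days faster when follow-up stops after one transfer, and slightly slower when all transfers count. The freezing delay is already included.

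**With some biopsy harm.** If biopsy lowers success by a relative 10% (q = 0.45 with PGT-A), all transfers give 43.8% in controls against 1 − (1 − 0.35 × 0.45)³ = 40.2% with PGT-A. The first transfer still shows 17.5% against 0.7254 × 0.45 = 32.6%.

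**The case against.** The strongest reply has four parts.

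1. A reader might infer that miscarriage and live birth cannot be measured at all. The documents do not support that. Section 6.5 asks women to report the pregnancy outcome, has them contacted if they do not, and says they consent to follow-up; Section 6.7 expects almost complete data. This part of the reply stands.
2. Section 6.5 does not say that the transfer it means is the first, and Section 6.4 speaks of later cycles. This stands as an ambiguity. It does not remove the conflict: read literally, a negative test ends the woman's pilot, and no section says that later transfers are counted. Mandatory reporting to the regulator supplies a data source but does not define which transfers belong to the endpoint.
3. A reader might infer that failures will be censored because they failed, or that every PGT-A transfer comes later than every control transfer. Neither is stated. Survival analysis is only named as an option in Sections 6.9 and 7, censoring rules may sit in an analysis plan that is not shown, and Section 6.3 allows controls a frozen first transfer.
4. A reader might take the tilt towards PGT-A as established. It is not: it depends on the first-transfer reading, on surplus embryos and on assumed rates, and the equal cumulative rates follow from the model. The freezing delay and women with no transferable embryo work against PGT-A; the illustration includes both, but their real size is unknown.

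The authors also explain in Sections 1.2 and 2 why they do not favour cumulative live birth as a measure. That is a defensible choice, but they chose a time endpoint themselves, and that endpoint needs later transfers to be observed.

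**Conclusion.** The conflict between Section 6.5 and the time endpoint in Section 5 is real. As written, a negative test ends a woman's pilot, and nothing restores follow-up of her remaining embryos. On the natural first-transfer reading, the endpoint then measures first-transfer success and the freezing delay. With two or more blastocysts, and under the assumptions above, that favours PGT-A even where the arms do equally well over all transfers; the size is illustrative and not an estimate for this trial.

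For miscarriage and live birth after a positive scan, the problem is inconsistent wording only. Severity is moderate: the primary outcome in Section 4 (recruitment, randomisation, adherence) and the recruitment threshold in Section 6.9 are untouched. The point gains weight from the plan to reuse pilot data and to let preliminary trends inform continuation.

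**What to change.** Reconcile Section 6.5 with Section 5:
- Limit the pilot-endpoint wording to the feasibility and clinical-pregnancy outcomes, and state that pregnancy outcomes reported after the scan feed the miscarriage and time endpoints.
- For the time endpoint, record every fresh and frozen transfer from the index egg collection in both arms, from randomisation over one common, prespecified window.
- Follow each pregnancy begun in that window to its outcome.
- Keep women without a transfer, or with no embryos left, in the denominator and in the risk set to the end of the window.

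The cost is some protocol wording, a few extra eCRF dates, possibly an amendment submitted to the ethics committee, and later secondary clinical results. Clinics must already report treatment outcomes, so the extra data burden is small. The feasibility report at 18 months need not wait.
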